### Trial intervention

The total duration of the trial will be 40 weeks, comprising a 16-week intervention phase and follow-up 24 weeks later. During the intervention phase all groups (AIT, TCT and COU) will be offered lifestyle counselling, alongside which the two exercise groups (AIT and TCT) will take part in a supervised physical exercise programme.

#### Counselling programme

The counselling programme consists of six, 50-min group sessions and three individual sessions lasting 40–50 min each. All these sessions will be conducted at the primary healthcare centre by a nurse trained in physical activity, nutrition and psychological strategies for behaviour change. An interactive participants’ guide has been published with the aim of reinforcing the counselling programme [25]. As a general rule, participants will be required, before the sessions, to read certain information (reports or chapters from the guide) or to reflect on the process of behaviour change. These aspects will then be discussed during the group or the individual meetings. Table 1 shows a detailed outline of the aims and activities of these meetings.

**Table 1 Tab1:** Aims and activities of healthy lifestyle counselling sessions for all interventions

N	Aims of the session	Example of meeting activities/actions *(Participant actions unless otherwise specified)*	
1^st^ Group Session (week 1)	To explain the programme To connect with the rest of the group and establish the dynamics of the meetings To become aware of the benefits of a healthy lifestyle To establish personal goals limiting the time spent in sedentary behaviours	Before the session	1. Browse the BELLUGA’T guide promoting a healthy lifestyle. 2. Review the schedule and the programme plan.
		During the session	Leader’s action: 1. Present the programme: structure, dates, goals, strategies, etc. 2. Introduce ice-breaker and rapport-building activities. Participant’s action: 1. Discuss beneficial effects of a healthy lifestyle. 2. Propose actions to reduce time spent in sedentary behaviours.
		After the session	1. Read the guide’s article about encouraging a healthier lifestyle. 2. Establish personal goals to reduce time spent in sedentary behaviors, based on ideas listed during group session.
1^st^ Individual Session (week 2)	To become aware of the effect of his/her cardiovascular risk factors on his/her health status To establish personal goals for controlling his/her risk factors and plan for the actions needed to succeed in achieving those goals	Before the session	Leader’s action: 1. Email results of baseline tests within 48 h of 1^st^ session. Participant’s action: 1. Read reports of basal tests. 2. Read the guide’s article about metabolic risk factors.
		During the session	1. Discuss reports with the leader. 2. Discuss personal risk factors and establish personal goals for the short (2 weeks), mid (16 weeks), and long term (40 weeks). 3. Select actions to achieve personal goals to reduce metabolic risk factors.
		After the session	1. Place actions needed to achieve risk factor goals in a visible place and start putting them into practice.
2^nd^ Group Session (week 4)	To become aware of the importance of a good workout To establish personal goals to increase physical activity	Before the meeting	1. Read guide’s article about increasing physical activity. 2. Reassess personal level of physical activity according to the reported accelerometer data (guide).
		During the session	Leader’s action: 1. Provide information about ways to achieve a physically active lifestyle. 2. Present specific information about training, hydration, and stretching. 3. Introduce digital resources to help participants be more active. Participant’s action: 1. Discuss beneficial effects of physical exercise in addition to routine physical activity. 2. Brainstorm examples of physical activities and exercise programmes
		After the session	1. Establish physical activity plan to be more active at work and in spare time in the next week. 2. Record physical activity in the smartphone application (app) or on paper.
3^rd^ Group Session (week 7)	To become aware of the possibilities of exercising at home, at work and in spare time using everyday items To establish personal goals to increase physical exercise	Before the meeting	1. Read and watch the video from the guide about tips to be more active at home.
		During the session	Leader’s action: 1. Demonstrate aerobic and strength exercises using stretch bands, dumbbells and improvised exercise material. Participant’s action: 1. Work on aerobic and strength exercises with improvised materials. 2. Share ideas and discuss ways of incorporating physical exercise into daily routines.
		After the session	1. Review the video of the aerobic and strength exercises practiced in class. 2. Establish physical exercise goals and record them in the app or on paper.
4 ^rd^ Group Session (week 10)	To become aware of the importance of good nutrition To establish personal goals to achieve good nutrition	Before the meeting	1. Read the guide’s article about healthy food choices.
		During the session	Leader’s action: 1. Provide nformation about healthy benefits of healthy eating. 2. Present the healthy food pyramid and the Mediterranean diet concept. Participant’s action: 1. Discuss the beneficial effects of healthy nutrition. 2. Brainstorm different ways of making healthy food choices.
		After the session	1. Identify unhealthy food choices made and record them in the app or on paper.
2^nd^ Individual Session (week 12)	To assess the current routine of physical activity and exercise and establish new strategies if necessary To become aware of the effect of good nutrition on his/her health status To establish personal nutritional goals and the actions needed to achieve them	Before the meeting	Leader’s action: 1. Email results of baseline dietary habits questionnaire within 48 h of 2^nd^ session. Participant’s action: 1. Carry out a self-assessment of the establishment of physical activity/exercise goals and the progress made. 2. Read report of baseline dietary habits questionnaire. 3. Read the guide’s article about strategies to overcome nutritional barriers.
		During the session	1. Review progress and resolve problems or setbacks in active lifestyle goal-setting and action planning. 2. Highlight positive changes and define potential ways forward, building on successes. 3. Discuss the dietary habits report with the leader and agree on personal goals. 4. Identify possible barriers to healthy eating and select actions/strategies to overcome them.
		After the session	1. Develop physical activity and exercise plan for the upcoming weeks. 2. Place actions needed to achieve active lifestyle goals in a visible place and start putting them into practice.
6^rd^ Group Session (week 16)	To become aware of barriers to new activity and nutritional behaviors and devise strategies to overcome them To establish new strategies to overcome barriers and maintain a new healthy lifestyle	Before the meeting	1. Read guide’s article about other healthy habits such as sleep and rest, reduce stress, no smoking, etc. 2. Review goals and think about new actions to overcome barriers.
		During the session	Leader’s action: 1. Provide information about maintaining a healthy lifestyle. 2. Resolve doubts and facilitate access to additional resources that may be needed. Participant’s action: 1. Share strategies to overcome barriers to new active lifestyle and dietary habits. 2. Brainstorm ideas to use the physical and social environment to become healthier.
		After the session	1. Review materials, acquired knowledge and strategies. 2. Think about how to apply them in oneself current situation.
3^rd^ Individual Session (weeks 18–19)	To become aware of the effects of oneself new lifestyle on reducing cardiovascular risk factors To establish new weekly personal goals for the next 6 months	Before the meeting	Leader’s action: 1. Email results of post-intervention tests within 48 h of 1^st^ session. Participant’s action: 1. Read the email reports of post-intervention results. 2. Review initial metabolic risk factors results emailed after 1^st^ group session.
		During the session	1. Analyse progress based on 16-week follow-up report after 16 weeks) and resolve problems or setbacks. 2. Highlight positive changes and discuss potential ways forward. 3. Agree on relapse prevention plans (active lifestyle and healthy eating) for the next 6 months.
		After the session	1. Maintain a new healthy lifestyle. 2. Keep a log of physical activity/exercise and eating habits, supported by the BELLUGA’T app. 3. Consult the programme guide, other educational material provided, and physical activity or primary healthcare professionals, as needed.

##### Group counselling sessions

Group sessions involving no more than 10 participants will be scheduled with the aim of providing counselling on a healthy lifestyle, including physical activity, sedentary behaviour and dietary habits. Strategies for behaviour change will also be introduced as a way of empowering participants. Additionally, these sessions will give participants the opportunity to receive peer support.

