#### Enrolment, screening and allocation

Participants will be recruited through primary healthcare centres, including physician referrals and advertisements through the media, community centres and electronic mailing. Interested individuals will be invited to an information session, where an in-depth detailed explanation of the study requirements and expectations will be given. Any questions will be answered and doubts clarified. Potential eligibility will be checked/confirmed by interview, obtaining information about age, past and current physical activity, medical history and medication use. Eligible participants who wish to participate in the study will be asked to sign written informed consent.

After providing written informed consent individuals will be given an identification number. Participants will be allocated to one of the two supervised physical exercise groups (AIT or TCT) or to the control group (COU), using a computer generated randomized list which allocates at random the identification number of the participant to a treatment group. The allocation sequence will be generated by the IDIAP and will be conducted without influence of the principal investigators.

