#### Supervised physical exercise

The supervised exercise programme will be offered to both exercise groups (AIT and TCT) and will consist of 16 supervised group training sessions lasting 50 min each and 32 non-supervised individual training sessions (i.e. self-administered by each participant).

The supervised training sessions will be run by experts in physical exercise (sports centre based), who will also deliver the instructions for the self-administered sessions.

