#### Statistical methods

An initial overview analysis will be carried out to detect any errors and to check the data for normality (Shapiro-Wilks test), this being done for all participants and intervention groups.

Intention-to-treat (ITT) analysis will be performed for all recruited participants who complete the baseline assessment, regardless of whether they subsequently complete the whole protocol. Missing outcome values will be replaced by data registered in the previous assessment using the last observation carried forward (LOCF) technique.

For the baseline comparison of groups we will use the chi-square test (or Fisher’s exact test) for categorical data and the analysis of variance (ANOVA) (or Kruskall-Wallis test) for quantitative data (continuous or ordinal). If significant differences are detected we will use Student’s *t*-test (or Mann–Whitney test) for each pair of groups.

For the analysis of the *intervention* effect two time frameworks will be established: efficacy (at the end of the intervention: t1) and durability (at 24-week follow-up: t2). Change will be calculated as the change from baseline values, both as absolute values and as a percentage adjusted to baseline values. We will adjust repeated measures techniques to study the general behaviour of the outcomes in the follow-up.

Continuous variables will be expressed as mean and standard deviation (SD). Effect size will be estimated as the mean standardized difference between the mean of each group divided by the pooled standard deviation. In accordance with Cohen’s criterion [54], values of 0.2–0.5 represent small differences, 0.5–0.8 moderate differences and >0.8 large differences. Categorical variables will be expressed as counts (n) and percentages (%), unless otherwise specified.

All analyses will be conducted using the Statistical Package for the Social Sciences (SPSS) v17 (SPSS Institute Inc., IL, USA) and the level of significance will be set at *p* < 0.05.

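### Participants are randomised individually but treated in groups, and neither the sample size nor the outcome analysis makes any allowance for delivery group

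*Protocol article*

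**What the plan says.** All of this is in the protocol article.

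- **Unit of randomisation** (Enrolment, screening and allocation): the individual. The list "allocates at random the identification number of the participant to a treatment group".
- **Counselling, all three arms** (Counselling programme): "The counselling programme consists of six, 50-min group sessions and three individual sessions lasting 40–50 min each". Under Group counselling sessions, "Group sessions involving no more than 10 participants will be scheduled", and "these sessions will give participants the opportunity to receive peer support". The article does not say whether a counselling group holds one arm only or a mixture.
- **Exercise, AIT and TCT only** (Supervised physical exercise): the programme "will consist of 16 supervised group training sessions lasting 50 min each and 32 non-supervised individual training sessions". Structure of the training sessions makes the main part different in the two arms. No size is given for a training group.
- **Sample size**: 35 per arm, 105 in total, from a 6.0 cm change in waist circumference (SD 5.3), two-sided alpha 0.05, beta 0.2 and 20% drop-out. There is no design effect and no intraclass correlation (ICC).
- **Statistical methods**: outcomes are analysed as change from baseline, and "We will adjust repeated measures techniques to study the general behaviour of the outcomes in the follow-up". Significance is at 0.05. No term for session group, leader or trainer is named. ANOVA and Student's t-test appear only for comparing the arms at baseline.

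**The concern.** People who attend the same sessions share a leader, a set of peers and a calendar period. Here the sharing is part of the intended mechanism, because peer support is a stated purpose of the counselling groups. Follow-up outcomes of members of one group may therefore resemble each other more than those of two arbitrary members of the same arm.

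If groups sit wholly within an arm, that shared component does not cancel in the comparison between arms. A model that knows only participants and visits then gives standard errors that are too small. AIT versus TCT is the most exposed comparison: their supervised sessions have different content, so their training groups are in effect separate, and both sides are clustered. It is also central to the general hypothesis.

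At stake are the true error rate of tests declared at 5% and the width of the confidence intervals. There is a practical point of timing too: group membership has to be recorded while sessions are running, and a later analysis plan may be unable to recover it.

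**Working it through.** **1. The plan's own figure.** Two-sample normal formula with the stated inputs:

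n per arm = 2 × (1.960 + 0.842)² × 5.3² / 6.0² = 12.25, so 13; with 20% drop-out, 13 / 0.8 = 16.25, so 17.

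The stated 35 is not reproduced from these inputs. That is a separate matter, but it means there is slack. After 20% drop-out, 35 × 0.8 = 28 per arm are evaluable, and 6.0 / (5.3 × √(2/28)) = 4.236, so power = Φ(4.236 − 1.960) ≈ 98.9%.

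**2. Inputs for clustering.** The article gives a cap of 10 per counselling group and 35 per arm, so if counselling groups are arm-specific there are at least four per arm (35 / 4 ≈ 9 in each). It gives no ICC; 0.01, 0.05 and 0.10 are assumed. It gives no training-group size, so 7 to 10 is also an assumption for those groups; larger ones would raise the design effect.

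**3. Both compared arms clustered, group ignored.** With group size m, design effect DE = 1 + (m − 1) × ICC. The true standard error is √DE times the unadjusted one, and the true error of a nominal 5% test is 2 × [1 − Φ(1.960 / √DE)].

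| ICC | m = 7: DE, error | m = 9: DE, error | m = 10: DE, error |
|---|---|---|---|
| 0.01 | 1.06, 5.7% | 1.08, 5.9% | 1.09, 6.0% |
| 0.05 | 1.30, 8.6% | 1.40, 9.8% | 1.45, 10.4% |
| 0.10 | 1.60, 12.1% | 1.80, 14.4% | 1.90, 15.5% |

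At m = 9 the true standard error is 1.04, 1.18 and 1.34 times the reported one.

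**4. Simulated two-sample t-tests** (40,000 to 60,000 replicates) under different layouts:

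| Layout | ICC 0.01 | ICC 0.05 | ICC 0.10 |
|---|---|---|---|
| Both arms, 35 each in groups of 10, 10, 10, 5 | 6.0% | 10.1% | 15.1% |
| Both arms, 28 each in four groups of 7 | 5.6% | 8.4% | 12.2% |
| One arm in four groups of 7, other arm unclustered | 5.3% | 6.6% | 8.6% |
| Groups mixing the arms evenly | 4.8% | 4.5% | 4.0% |

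The last row used nine groups with four from each arm. That is twelve per group, above the counselling cap; three from each arm gives practically the same result. At ICC 0 the error is 5%.

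**5. Power for 6.0 cm with 28 evaluable per arm**, dividing 4.236 by √DE at m = 10:

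- ICC 0.05: 4.236 / 1.204 = 3.518; Φ(3.518 − 1.960) ≈ 94%.
- ICC 0.10: 4.236 / 1.378 = 3.073; Φ(3.073 − 1.960) ≈ 87%.

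These use normal critical values. As a strict check, take four groups of 7 per arm and only 2 × (4 − 1) = 6 group-level degrees of freedom (critical value 2.447). At ICC 0.10 the non-centrality is 4.236 / √1.60 = 3.349, and power from the non-central t is about 80%.

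**The case against.** - **The point rests on silence.** No sentence says that participants are treated as independent, the outcome model is barely specified, and a separate analysis plan could add a group term. This stands against any claim that the plan asserts independence. It does not remove the point: the sample size is fixed without allowance, the methods section goes into detail on missing values, effect sizes and software without mentioning delivery group, and membership must be captured during delivery.
- **ANOVA and t-tests.** A reader might infer that outcomes will be compared by these tests. The article assigns them to the baseline comparison only, before any session has taken place.
- **Nesting of counselling groups is not stated.** This stands. If those groups mix arms evenly, ignoring them makes the test slightly conservative. Only the AIT and TCT training groups can be taken as arm-specific, and that is inferred from their differing content.
- **The cap of 10 belongs to counselling.** This stands; for training groups the size is assumed. COU has no training groups, so if counselling groups are mixed, AIT or TCT versus COU falls in the one-arm-clustered row.
- **Much of the delivery is individual.** Of 48 training sessions 32 are self-administered, and three of nine counselling sessions are one-to-one. That argues for a lower ICC, not for zero.
- **Loss of sample size.** A reader might divide 28 completers by the m = 9 design effects and get 26, 20 and 16 effective participants. That mixes two populations: m = 9 goes with 35 per arm in four groups, while 28 in four groups means m = 7 and about 26, 22 and 18. Nor do the figures show an underpowered trial for 6.0 cm.
- **The remedy is fragile.** With about four groups per arm the group variance is poorly estimated. This is true and shapes the fix.

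**Conclusion.** The point holds in conditional form. Randomisation is individual, delivery is in groups, at least the AIT and TCT training groups are in effect arm-specific, and neither the sample size nor the outcome analysis takes delivery group into account. If within-group correlation is positive, nominal 5% tests would run at roughly 6% to 15% for ICCs of 0.01 to 0.10 with groups of 9 to 10. Smaller groups, or clustering in only one of the two compared arms, bring the inflation down to the lower ranges shown above.

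The documents do not support saying flatly that standard errors are too small or that the 5% level fails. Both depend on an ICC that the article does not give and on nesting that it does not state for counselling.

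Power is not the main issue: it stays at about 87% or more up to ICC 0.10 on the normal approximation, and near 80% on the strict six-degree check. The consequence is for error rate and interval width. It is worth correcting but does not undermine the design.

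**What to change.** 1. Record, as sessions are delivered, each participant's counselling group and training group.
2. State whether counselling groups are arm-specific or mixed.
3. Fit the outcome model with a random intercept for arm-specific group, treating participants without such a group as their own cluster. Use small-sample degrees of freedom (Kenward-Roger or Satterthwaite, or group-level degrees of freedom if the named software offers neither).
4. Report the estimated ICC for each main outcome.
5. Because about four groups per arm say little about the group variance, add a sensitivity analysis that fixes the ICC at stated values, for example 0.01, 0.05 and 0.10, and shows the interval at each.
6. Give the detectable difference with and without the design effect.

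The cost is one or two variables in the data set, one model term and somewhat wider intervals. No increase beyond 35 per arm follows over this ICC range: with the m = 10 design effect at ICC 0.10 the formula in step 1 of the working gives 12.25 × 1.90 = 23.3, so 24 per arm, or 30 after drop-out.

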##### Individual sessions

The aim of the individual sessions will be to focus in greater depth on each participant’s needs. The professional will help the participant to establish realistic daily goals for physical activity and will involve him/her in the decision-making process. The session will be based on the transtheoretical model of behaviour-change [26] and on motivational interviewing [27].

#### Supervised physical exercise

The supervised exercise programme will be offered to both exercise groups (AIT and TCT) and will consist of 16 supervised group training sessions lasting 50 min each and 32 non-supervised individual training sessions (i.e. self-administered by each participant).

The supervised training sessions will be run by experts in physical exercise (sports centre based), who will also deliver the instructions for the self-administered sessions.

##### Structure of the training sessions

All training lessons will comprise five parts: introduction (aims and contents), warm-up, main part (differing between the AIT and TCT groups, see below), cool-down, and stretching and conclusions (instructions for self-administered sessions).

The main part will differ between groups and consists of:AIT group: Four series of 4 min of cycling at a heart rate of 80% of the VO_2peak_ registered previously during the stress test, with active pauses of 2 min at 60% of the VO_2peak_ between them (Table 2).

**Table 2 Tab2:** Weekly schedule for the main part of the AIT program sessions

Week number	Supervised/self-administered lessons (n/n)	Content of the main part of the AIT sessions			
		Work volume (Rep x time)	Work Intensity (% VO_2peak_)	Active rest (time)	Total accumulated time
1	2/1	16 × 1’	80	30”	24’
2	2/1	8 × 2’	80	1’	24’
3	2/1	5 × 3’	80	2’	25’
4	2/1	4 × 4’	80	2’	24’
5	1/2	4 × 4’	80	2’	24’
6	1/2	4 × 4’	80	2’	24’
7	0/3	4 × 4’	80	2’	24’
8	1/2	4 × 4’	80	2’	24’
9	1/2	4 × 4’	80	2’	24’
10	0/3	4 × 4’	80	2’	24’
11	1/2	4 × 4’	80	2’	24’
12	1/2	4 × 4’	80	2’	24’
13	0/3	4 × 4’	80	2’	24’
14	1/2	4 × 4’	80	2’	24’
15	0/3	4 × 4’	80	2’	24’
16	1/2	4 × 4’	80	2’	24’

*AIT* aerobic interval training; n, number, *Rep* repetitions, *VO*
_*2peak*_, peak oxygen uptakeGiven that maintaining the anticipated exercise intensity might, at the beginning of the programme, excessively burden participants allocated to this group, the length of the series will be shorter during the initial sessions. Thus, intensity will be established at 80% of the VO_2peak_ but series will last for 1 min during the first week, after which they will be increased by 1 min each successive week until reaching a duration of four minutes. At the same time, active pauses will be shortened so as to accumulate an exercise time of 24 min in that part of the session.TCT group: Participants allocated to this group will perform activities such as walking, cycling, team activities and toning exercises, always at an intensity of 60% of their VO_2peak_. The number of training sessions per week and the ratio of supervised to self-administered sessions will be the same as that shown in Table 2 for the AIT group.

